#### Patient groups for data analysis

##### Intent-to-treat population

The ITT population will include all participants treated with at least one dose of the study drug and who keep and return a daily cough diary for at least one day of recordings.

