### Participants

#### Inclusion, exclusion, and withdrawal criteria

The inclusion criteria are: (1) age between 19 and 75 years; (2) chronic cough that has lasted more than 8 weeks; (3) dry cough (sputum frequency of 5 or fewer times per day, and sputum volume less than 10 ml per day, on the basis of the Sputum Severity Evaluation Standard of the Korean Ministry of Food and Drug Safety); (4) provision of written informed consent.

The exclusion criteria are: (1) abnormal pulmonary function test (forced vital capacity, or forced expiratory volume in 1 s, < 80 % of predicted); (2) abnormal chest X-ray; (3) acute respiratory disease, including upper respiratory tract infection, during the previous 4 weeks; (4) chronic pulmonary diseases (COPD, idiopathic pulmonary fibrosis, bronchiectasis, etc.) during the previous 2 years; (5) diagnosis of malignant tumor during the previous 5 years; (6) history of smoking (≥20 packs [400 cigarettes] during the participants’ lifetime); (7) treatment taking an angiotensin-converting-enzyme inhibitor at present or during the previous 4 months; (8) current or the precious 2-week use of antitussive drugs, glucocorticoids, leukotriene receptor antagonists, anticholinergic drugs, long-acting β2 agonists or any herbal medication; (9) antihistamine treatment during the previous 3 days; (10) aspartate aminotransferase (AST) or alanine aminotransferase (ALT) levels at least twofold higher than the upper normal limit, or a serum creatinine levels at least 1.2-fold the upper normal limit; (11) a mean cough diary score of less than 2 during the 1-week run-in period; (12) fewer than 10 entries in the cough diary during the 1-week run-in period; (13) pregnancy or breastfeeding; (14) illiteracy or cognitive impairment; (15) unsuitability as judged by the investigators.

The rejection and withdrawal criteria are: (1) treatment that might influence the results of the trial without the agreement of an investigator; (2) use of forbidden drugs, such as antitussives, glucocorticoids, leukotriene receptor antagonists, anticholinergics, and long-acting β2 agonists; (3) participants not following the protocol, or taking < 80 % of the prescribed doses; (4) a serious adverse event (SAE) during the trial; (5) voluntary withdrawal from the trial; (6) unsuitability as judged by the investigators.

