### Concomitant and forbidden drugs

If participants experience unbearable cough at night, taking one capsule acetylcysteine is permitted; this antitussive will be delivered to the patients along with the MMDT or placebo granules. If this does not improve the cough, the participant will visit the K-CTC for examination and appropriate management. The participants will be asked to record whether they take the antitussive agent or not. Other drugs that alleviate cough—such as other antitussives, glucocorticoids, leukotriene receptor antagonists, anticholinergics, short-acting β2 agonists, long-acting β2 agonists, and antihistamines—are prohibited. Drugs which are not related to cough symptoms will be permitted. The name, duration, and dosage of any other drugs taken will be recorded in the case report forms.

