### Statistical analysis plan

Data entry and management will be completed by an independent data administrator to ensure data accuracy. We will analyze the efficacy and safety of MMDT using the “intent-to-treat” (ITT) principle. Subordinately, we will also present the results of the analysis based on the “per protocol” principle.

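### The set labelled intent-to-treat depends on dosing and diary return, does not say which diary days count, and carries the diary condition into the safety analysis

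*Protocol article*

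**What the plan says.** Under Statistical analysis plan, the protocol article states: "We will analyze the efficacy and safety of MMDT using the “intent-to-treat” (ITT) principle". A per-protocol analysis is secondary.

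Under Intent-to-treat population, the set is "participants treated with at least one dose of the study drug and who keep and return a daily cough diary", and the diary need cover only one day ("for at least one day of recordings"). The only other groups defined are the per-protocol population and the MMDT responder and non-responder groups. No separate safety population appears.

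Four other places bear on this:

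- **Safety outcomes.** Safety is judged from adverse reaction reports and laboratory tests, not from the diary.
- **Inclusion, exclusion, and withdrawal criteria.** Fewer than 10 diary entries in the run-in week excludes a patient. The same section lists grounds for rejection or withdrawal. These include "participants not following the protocol, or taking" under 80% of doses, "use of forbidden drugs, such as antitussives, glucocorticoids, leukotriene receptor antagonists, anticholinergics" and long-acting β2 agonists, and a serious adverse event.
- **Concomitant and forbidden drugs.** For unbearable night cough, "taking one capsule acetylcysteine is permitted; this antitussive will be delivered to the patients". Other antitussives are prohibited.
- **Statistical analysis.** Missing values are filled by last observation carried forward (LOCF).

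**The concern.** An ITT analysis keeps everyone who was randomised, in the arm assigned. Here two events after allocation decide membership: taking a dose, and keeping and returning a diary. The dose condition is the milder of the two, because participants and investigators are blinded. Diary return is the greater worry. It can depend on how well the treatment works and how well it is tolerated, and so on the arm. If it does, the comparison of those kept is no longer protected by randomisation.

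For safety the condition has no rationale. Whether a treated participant had an adverse event or an abnormal laboratory value does not depend on a returned cough diary. Someone who stops early because of an adverse event is a plausible non-returner, and a serious adverse event is itself a withdrawal criterion. The set used to count harms could therefore omit participants who matter for that count.

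**Working it through.** **1. The plan's own figure.** Inputs from Sample size calculation: effect size 0.85, 20% dropout, 1:1 allocation; two-sided alpha 0.05 and power 0.80 are stated beside the 0.699 effect size. A two-sample t-test (noncentral t) needs 22.73, so 23 per arm. Then 23 / (1 − 0.20) = 28.75, so 29 per arm and 58 in total. The stated 58 reproduces; no arithmetic error is alleged.

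**2. Two readings of the diary day.**

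- *Run-in days count.* Everyone randomised has at least 10 run-in entries. With at most two entries a day (daytime and night-time), that is at least 10 / 2 = 5 days, so the one-day requirement is already met. The run-in diary must also have been seen, since it decides eligibility and supplies the baseline score. The diary condition then excludes almost nobody, but LOCF could carry a pre-treatment score to week 4.
- *Only days after randomisation count.* Table 1 hands out a diary card at visit 1 and next records the diary score at visit 2 (week 2). Anyone who leaves in between without returning that card is outside the set for both efficacy and safety.

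The text does not choose between them.

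**3. Weight of one participant.** 1 / 29 = 3.4% of an arm. Hypothetically, one event among 29 treated is 1/29 = 3.4%; if that participant is outside the set, the arm shows 0/28 = 0%.

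**4. Range for efficacy and safety.** The documents give no excluded share, so q is an assumption, taken from 5% to 20% in each arm. Suppose also that the effect is 0.85 among those kept, that those excluded gain nothing, and that the SD is unchanged. The all-randomised effect is then 0.85 × (1 − q). The last column is the 95% upper bound for an event not seen in the n kept, 1 − 0.05^(1/n).

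| q | Kept per arm | Power in those kept (0.85) | All-randomised effect | Power, 29 per arm | Bound, zero events |
|---|---|---|---|---|---|
| 0 | 29 | 0.889 | 0.85 | 0.889 | 9.8% |
| 5% | 28 | 0.878 | 0.81 | 0.86 | 10.1% |
| 10% | 26 | 0.852 | 0.77 | 0.82 | 10.9% |
| 20% | 23 | 0.805 | 0.68 | 0.72 | 12.2% |

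The gap between the effect in those kept and in all randomised is 0.85 × 0.05 = 0.04 SD at the low end and 0.85 × 0.20 = 0.17 SD at the high end. The safety bound shows loss of precision only; it does not measure bias from losing participants who had events.

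**5. Withdrawal against membership.** Taking under 80% of doses is a ground for withdrawal. ITT membership needs one dose and one diary day, and LOCF fills what is missing. A withdrawn participant who meets those two conditions stays in the set. Withdrawal can affect the outcome data, not membership.

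**The case against.** The strongest reply is that exclusion is possible, not established. If run-in days count, the diary condition is almost empty and the treated participant with an early adverse event stays in the safety analysis. That is right, and it is why the defect is stated as an unclear definition with a possible exclusion. It does not save the wording: a primary population that supports both readings is badly fixed, and the set is not ITT under either, because a dose is still required.

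A second reply is that adverse events are monitored continuously, so an early event would be recorded. It may well be. But recording an event does not put the participant into the set in which safety is analysed.

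Three stronger readings are tempting and are not supported:

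- *The withdrawal criteria make ITT nearly the same as per-protocol.* No section removes withdrawn participants from the ITT set. Table 1 checks compliance at weeks 2 and 4, the visits at which the diary score is also recorded, so someone found below 80% at week 4 has reached the primary assessment. That diary collection stops at withdrawal is an inference; the text is silent.
- *Permitted rescue use triggers withdrawal.* The withdrawal list names antitussives without an exception. However, Concomitant and forbidden drugs expressly permits the capsule and forbids only other antitussives. A cross-reference would help; there is no real contradiction.
- *The 20% dropout allowance, 0.20 × 58 = 11.6 or about 12 participants, measures the exclusion.* It is an allowance for missing data already built into the 58, not a count of those outside the ITT set.

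**Conclusion.** The point holds in limited form. The population named ITT is a modified ITT set conditioned on dosing and diary return. Its diary day is not tied to a period, and it is the only stated set for safety, where a diary condition has no place. A reader might infer that neither efficacy nor safety will be analysed as claimed, or that harms will be undercounted. The documents do not support that: they give no number of non-returners, and under the run-in reading almost nobody is lost to the diary condition.

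The known size is 3.4% of an arm per participant excluded. The 0.04 to 0.17 SD gap rests on an assumed 5% to 20% exclusion with no benefit in those excluded. In an exploratory single-centre trial whose sample size reproduces, this should be fixed, but it does not invalidate the design.

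**What to change.** 1. Under Intent-to-treat population, define the primary efficacy set as all randomised participants, analysed as allocated. If the present set is wanted, keep it as a sensitivity set, call it modified ITT, and say whether the diary day must follow randomisation.
2. Add a safety set: everyone who took at least one dose, with no diary condition. Change the sentence under Statistical analysis plan so that safety refers to this set.
3. Reconcile the rejection and withdrawal criteria with the ITT principle by stating whether data collection and analysis continue for participants who meet them. The clinical content of those criteria is for the investigators.
4. Let the withdrawal list cross-refer to the drug permitted under Concomitant and forbidden drugs.

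The cost is minor wording and possibly a few more imputed values in the primary analysis. Under the stated LOCF rule, a participant with no on-treatment diary would enter week 4 with the run-in score. No adverse-event check or safety test beyond those in Table 1 is asked for.

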##### Per-protocol population

The per-protocol population will include patients who take more than 80 % of the prescribed doses of the study drug, fill in the daily cough diary on 80 % of the study days, and return their diary to the researchers.

##### MMDT responder/non-responder groups

An MMDT treatment responder is defined as a participant who exhibits a 75 % decrease in cough diary score after 4 weeks of treatment; all other participants in the MMDT treatment group will be included in the non-responder group. We will analyze the correlations between MMDT responder group and all TKM patterns.

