### Randomization and Concealment

An independent statistician who is unware of the design and purpose of the study will generate a randomization table using R software (version 3.2.0; The R Foundation for Statistical Computing); specifically, a block size of 4 will be used, and the 58 patients will be randomly allocated group in a 1:1 ratio either to the MMDT treatment group or to the placebo control. The statistician will keep the randomization lists and inform the researcher of the matching cord number either by text message or via mobile communication application.

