##### Pattern Identification for Chronic Cough Questionnaire

The Pattern Identification for Chronic Cough Questionnaire (PICCQ) is used to identify patterns in chronic cough patients. We developed this questionnaire using the Delphi method [32], and conducted clinical research to confirm its validity and reliability. The PICCQ consists of four patterns: wind-cold, phlegm-turbidity, fire-heat, and deficiency (lung deficiency and kidney yang deficiency). The PICCQ comprises 38 items scored on 5-point Likert scales. A patient’s pattern is calculated by summing the scores of each item. We will investigate the chronic cough pattern distribution in chronic dry cough patients, as well as the correlation between chronic cough pattern and the efficacy of MMDT.

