##### Yin Deficiency Scale

We will use the validated *yin* deficiency scale developed by Park [34]. This questionnaire consists of 27 items, each of which uses a 7-point Likert scale; the cut-off point was defined as 10 points. We will use the *yin* deficiency scale to evaluate chronic dry cough patients, as well as to investigate the correlation between the *yin* deficiency pattern and the efficacy of MMDT.

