### Statistical analysis

Descriptive statistics will be used for continuous variables, and frequencies for categorical variables. The “last observation carried forward” (LOCF) principle will be used to compensate for missing data. The LOCF principle involves replacement of missing data with the last observed value to obtain a complete database.

When the assumption of normality is satisfied will a *t*-test be used to compare the two groups in terms of the primary outcome (mean cough diary score at week 4). Otherwise, the Mann–Whitney *U*-test will be used. Other continuous variables, such as mean efficacy measurements (cough VAS score or LCQ scores), safety tests (AST, ALT, ALP, TB, GGT, BUN, creatinine, sodium or potassium levels), and biomarkers will be analyzed using the same statistical methods. Associations between the MMDT responders and non-responders with regard to each identified pattern will be estimated using a logistic regression model, which will be adjusted for covariates. All data will be analyzed using SPSS™ for Windows software. The level of significance will be set at a two-sided P value of 0.05.

We, along with a professional statistician, will perform the data analysis for the results.

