## Discussion

Chronic cough is a common symptom in respiratory outpatients, and in an increasing number, the symptom is not eased by conventional treatments. Recent studies have found that substantially fewer patients now respond fully to treatment [7, 37, 38]. Due to the increased patients and limited treatment options, chronic cough is considered a challenging clinical problem.

MMDT is a traditional herbal medicine that has long been used to treat chronic dry cough; however, the evidence regarding the medicine’s efficacy is sparse. We aim to demonstrate the efficacy and safety of MMDT in chronic dry cough via a randomized, placebo-controlled clinical trial that has been designed in accordance with the Consolidated Standards of Reporting Trials guidelines [39]. In addition, we will investigate the relationship between the specifically identified pattern of cough and the effectiveness of MMDT. This trial will provide high-quality evidence on the efficacy and safety of MMDT in the treatment of chronic dry cough. A larger-scale clinical trial to evaluate the effectiveness and safety of MMDT in treating chronic dry cough, based on this study and with specific cough patterns identified, will be possible in future.

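### The link between pattern and MMDT efficacy is tested inside the MMDT arm only, so a prognostic pattern cannot be told from one that modifies the effect of MMDT

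*Protocol article*

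**What the plan says.** The aim is worded as efficacy. The section on the Pattern Identification for Chronic Cough Questionnaire plans to study pattern distribution "as well as the correlation between chronic cough pattern and the efficacy of MMDT". The Cold-Heat Pattern Questionnaire and Yin Deficiency Scale sections state the same aim for their own scores. The Discussion repeats it: "we will investigate the relationship between the specifically identified pattern of cough and the effectiveness of MMDT".

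The method is given in two places. Under MMDT responder/non-responder groups, a responder is "a participant who exhibits a 75 % decrease in cough diary score after 4 weeks of treatment", and "all other participants in the MMDT treatment group will be included in the non-responder group". The same section adds: "We will analyze the correlations between MMDT responder group and all TKM patterns". Under Statistical analysis: "Associations between the MMDT responders and non-responders with regard to each identified pattern will be estimated using a logistic regression model", with adjustment for covariates.

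Participants are "randomly allocated group in a 1:1 ratio either to the MMDT treatment group or to the placebo control" (Randomization and Concealment). Table 1 is a single schedule with no distinction by arm. It places all three pattern scales at visits 1 and 3, and the cough diary score at visits 1, 2, 3 and follow-up. No section plans a placebo responder group, an MMDT-placebo comparison within patterns, or an arm-by-pattern term.

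**The concern.** In a placebo-controlled trial, efficacy means benefit over placebo. Response here is a within-patient fall in the diary score. That fall mixes any drug effect with natural course, regression to the mean and placebo response. If one of these differs by pattern, the pattern will be associated with response in the MMDT arm even when MMDT does nothing, or does equally much in every pattern.

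At stake is the interpretation of the pattern results. The Discussion foresees a larger trial that builds on this one with cough patterns identified. A pattern that merely marks a better course could be carried forward as one in which MMDT works, although the randomised data needed to check this are already scheduled.

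**Working it through.** **The plan's own figure.** The claim disputes no stated number, but N reproduces. For a two-sample t-test with d = 0.85, two-sided alpha 0.05 and power 0.80, n = 22.73, so 23 per arm. Then 23/(1 − 0.20) = 28.75, so 29 per arm and 58 in total, as stated under Sample size calculation.

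**What the one-arm model estimates.** Let p(a,k) be the responder probability in arm a (M = MMDT, P = placebo) for pattern k (1 = present, 0 = absent). The planned log odds ratio is

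logit p(M,1) − logit p(M,0) = [logit p(P,1) − logit p(P,0)] + {[logit p(M,1) − logit p(P,1)] − [logit p(M,0) − logit p(P,0)]}.

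The first bracket is prognosis and the braces hold effect modification. One arm gives only their sum.

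Example with assumed rates of 10 % and 40 % in the MMDT arm: OR = (0.40/0.60)/(0.10/0.90) = 6.0.
- Placebo also 10 % and 40 %: placebo OR 6.0, ratio of odds ratios 6.0/6.0 = 1. The pattern is purely prognostic.
- Placebo 10 % and 10 %: placebo OR 1.0, ratio 6.0/1.0 = 6. The pattern purely modifies the effect.

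The planned analysis sees identical data in both cases. Simulation at 23 to 29 per arm agrees: the one-arm likelihood-ratio test rejects in 43-52 % of trials in the first case and 44-51 % in the second. The two-arm interaction test rejects in 6-7 % and 22-25 %.

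**How often a purely prognostic pattern would look like efficacy.** Assumed, since the documents give none of these: 29 per arm, binary pattern at 50 %, baseline 5 (SD 1.5), residual SD 1.5, inert MMDT, and a pattern worth 1, 1.5 or 2 points of improvement in both arms. The 75 % responder rule is the protocol's. Rejection rates of the one-arm test, from 3,000 to 4,000 simulated trials per cell:

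| Background improvement | Test | 1 point | 1.5 points | 2 points |
|---|---|---|---|---|
| 1 point | Likelihood ratio | 17 % | 32 % | 53 % |
| 1 point | Fisher | 5 % | 15 % | 34 % |
| 0 | Likelihood ratio | 5 % | 15 % | 33 % |
| 0 | Fisher | 1 % | 3 % | 10 % |

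The arm-by-pattern interaction on the week-4 score, adjusted for baseline, rejects in about 5-6 %. Fisher's test is conservative at this size: with equal responder rates of 25 %, it rejects in 2-3 % of trials, against 6-7 % for the likelihood-ratio test.

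**Precision of the two-arm analysis.** For a 50:50 pattern with N/4 per cell, the interaction variance is 4 × SD²/(N/4) = 16 SD²/N.
- N = 58: SE = √(16/58) = 0.53 SD; 95 % CI half-width 1.96 × 0.525 = 1.03 SD; power for 0.85 SD = Φ(0.85/0.525 − 1.96) = 37 %.
- N = 46 (after 20 % dropout): SE = √(16/46) = 0.59 SD; half-width 1.16 SD; power 30 %.

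**The case against.** The best case for leaving the plan alone is that the trial calls itself exploratory, its hypothesis and primary outcome are tested between arms, and this is one subordinate association. That stands and limits the severity.

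A reader might infer that all natural course, regression to the mean and placebo response in the MMDT arm will be read as pattern-specific efficacy. The documents do not support this. Whatever is equal across patterns creates no association between pattern and response, and nothing in the protocol shows that any pattern is prognostic. The entry cut-off is also a weak source of regression to the mean on the assumed inputs. With mean 5, SD 1.5 and cut-off 2, z = −2, so about 2.3 % are truncated and the mean shifts by 1.5 × 0.054/0.977 = 0.08 points. The single-day baseline adds noise, but it too matters only if its effect differs by pattern.

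A reader might also infer that the next trial will be restricted to the patterns found here. The Discussion says only that a larger trial with patterns identified will be possible; it gives no selection rule.

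The rejection rates can fairly be called assumption-driven. They need a pattern effect of 0.67 to 1.33 residual SD (1/1.5 to 2/1.5), they move with background improvement and test, and they reduce multi-item scores to one binary. They also omit the planned covariate adjustment. That adjustment does not answer the objection, because covariates within one arm cannot supply the missing placebo contrast. Nor does the condensed format of an article: the MMDT-only comparison is an explicit choice, not an omitted detail.

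**Conclusion.** The point holds in this limited form. The stated method does not estimate the stated quantity: an association within the MMDT arm cannot separate a prognostic pattern from one that modifies the effect of MMDT. That follows from the structure of the analysis and needs no assumed values. How often it would mislead here is unknown. The 5-53 % is an illustration under the assumptions listed, spanning the first three rows of the table; the fourth is lower. It is not the risk in this trial.

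A conclusion that the efficacy result of the trial is compromised would go too far. The primary week-4 comparison is between randomised arms, and neither it nor N = 58 depends on the responder analysis. This should be fixed, as an exploratory secondary analysis.

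**What to change.** Under MMDT responder/non-responder groups, define response identically in both arms. Under Statistical analysis, add a model on all randomised participants: week-4 diary score on arm, baseline diary score, visit-1 pattern score and arm-by-pattern interaction. Report MMDT-placebo differences by pattern with 95 % CIs, marked as exploratory. The MMDT-only logistic model may stay if it is labelled as not showing pattern-specific efficacy.

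The cost is a change of analysis wording; Table 1 already schedules the data. The price is precision: a CI half-width of about 1.0 to 1.2 SD and 30-37 % power for an interaction of 0.85 SD. The text should therefore say that a null interaction is not evidence that the effect of MMDT is the same in every pattern.
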